## Methods

### Participants

A total of 166 outpatients will be recruited in one center (Neuropsychiatric Center of Hamburg), following the invitation of their treating physician or psychotherapist, to use a new method to measure their mental state and distress. Inclusion and exclusion criteria for the study are listed in Textbox 1.

Inclusion and exclusion criteria.Inclusion criteria:A regular outpatient with a mental disorder or neurological diseaseNative German speakerAged 18-65 years oldIn good general health (absence of cancer, acute myocardial infarction, unstable angina, severe cardiac arrhythmia, recent cerebrovascular incident, or severe atherosclerosis).Exclusion criteria:SchizophreniaDementiaCurrent or recent (less than 1 year) history of alcohol or drug abuseCurrent or recent (less than 1 year) history of suicide attemptsOther significant comorbidities according to the Investigator’s clinical assessment (eg, cancer, acute myocardial infarction, unstable angina, severe cardiac arrhythmia, recent cerebrovascular incident, or severe atherosclerosis).

For the exclusion criteria, both schizophrenia and dementia have shown indications that a patient’s speech patterns are influenced by these disorders. Therefore, we decided to consider these two groups of patients separately in a future study to see whether there is a comparable difference to the general population on a content-free linguistic level.

### Linguistic Algorithm and Recording System

#### Audio Collection

Speech utterances of the subjects will be sampled using the VoiceSense mobile app, which will be installed on the tablets (BENEVE Co, 10.1-inch screen, 32 gigabytes of memory, Android version 7.0) of the research examiners. The recordings will be taken over 1-3 separate sessions throughout the study: the initial interview, the first follow-up session after 2-4 weeks, and the second follow-up session after another 2-4 week period. In each of those sessions, the research examiners will activate the app by logging into it with a dedicated username and password that was prepared in advance for each subject (the username and password do not reveal the subject’s identification). The app then presents 9 general questions (eg, “Please describe in a few sentences how was your day yesterday”). The subject presses record and answers, and when finished they will press stop and the app will present a second question for the subject to answer. The app will count the recorded time to verify that at least 120 seconds are recorded, but if after nine answers there is still not enough recording time then the app will present an increasing number of questions till the time requirement is met. Once enough speech is recorded, the app will send the recorded audio to the VoiceSense cloud server for analysis. The content of the subject’s answers is not important for the analysis; therefore, the questions are designed in a general manner to enable collection of the natural speech patterns of the subjects. The recordings will be done in a quiet room in the Neuropsychiatric Center Hamburg, which is reserved for diagnostic purposes. The examiner will leave the room while the recording is done, to make the subjects feel more comfortable and to not influence their free speech.

#### Speech Analysis

The audio that will be sent to the server will be analyzed using VoiceSense proprietary speech analysis. This analysis produces raw data of over 200 prosodic parameters for each call. The raw data parameters will be sent back to the research center for the statistical analysis, with a sampling frequency of 8 kilohertz.

VoiceSense speech analysis focuses on speech prosody, the noncontent aspects of the speech, such as intonation, pace, stressing, and other aspects. The analysis is language independent and has been tested successfully in many languages (different European languages, different Asian languages, etc). The analysis was validated versus various personality tools, such as Big 5 [23], Holland [24], Hogan [25], WPI [26], and linked speech patterns (clusters of the raw speech parameters) with the personality scales as measured by these tools. The analysis is based on several granted patents regarding measurement of emotional state [27] and behavioral tendencies [28] through speech analysis. This proprietary speech anal ysis is the basis for commercial products in the fields of enterprise, big data analytics, customer analytics, human resources, and others.

### Study Design and Data Protection

This study is a case-controlled study with a case group and a control group to identify the best target population for measuring speech patterns with the VoiceSense app. We adhered to the Consolidated Standards of Reporting Trials (CONSORT) guidelines in the design of the trial.

In the first step, the participants will be grouped by the physician or psychotherapist into a control group (participants without mental disorders) or a case group (participants with mental disorders). All participants will provide written informed consent after being given detailed information by the treating therapist or physician. The original forms will be stored in a closed cabinet, but the participants will receive a copy. Second, they will receive a pseudonymized label for the blinded inhouse-rater to work with the questionnaires, and for the data center for the speech-analysis. Neither the rater nor the data center will know the name and diagnosis of the participant. Data security and availability will be ensured every time, according to the European Union (EU) rules [29]. The participants’ data will be stored in a MySQL-Database. Within the project database, identifying data will be stored separately from the collected data, with only project staff with specifically conferred access rights able to access the identifying data. It is envisioned that the distribution of participants will correspond to the clinical distribution in the Neuropsychiatric Center with different degrees of severity of mental disorders (about 25% mild, about 50% moderate, about 25% severe). This should be checked by the study nurse every 2 weeks.

For documentation purposes, the presence or absence (in the case of neurological outpatients) of any psychiatric diagnosis will be screened using the PHQ-D [30]. Personality traits will then be measured with the Big 5 Test [23]. In the case of ADHD, we added a Visual Analogue Scale (ADHD-VAS) to identify the three main affective states (impulsivity, inattention, and hyperactivity). This will be done at baseline only.

At baseline, at follow-up one (2-4 weeks after baseline), and follow-up two (2-4 weeks after follow-up 1), participants will be measured for mental distress using the SCL-90 [31]. They will then be asked to freely answer nine standardized questions, with a few sentences per question. These answers will be recorded for evaluation. If less than 120 seconds of free speech is possible, three more standardized questions will be asked and the answers to these will also be recorded. The recorded sentences will then be sent to the server to carry out the prosodic analysis. The results of the questionnaires and the results of the prosodic analysis will be stored in the patients’ records on file. Figure 1 shows the flow chart of the study.

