**Methods:**

In this paper, we described a case-controlled study (with a case group and one control group). The participants will be recruited in an outpatient neuropsychiatric treatment center. Inclusion criteria are a neurological or psychiatric diagnosis made by a specialist, no terminal or life-threatening illnesses, and fluent use of the German language. Exclusion criteria include psychosis, dementia, speech or language disorders in neurological diseases, addiction history, a suicide attempt recently or in the last 12 months, or insufficient language skills. The measuring instrument will be the VoiceSense digital voice analysis tool, which enables the analysis of 200 specific speech parameters, and the assessment of findings using psychometric instruments and questionnaires (SCL-90, PHQ, Big 5 Test).

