### Statistical Methods

It should be possible for the study team to evaluate the efficacy and effectiveness of the raw data from the linguistic analysis in correlation with the clinical data collected with the questionnaires. All statistical tests will be two-tailed and will be considered statistically significant at *P*<.05. A sample size of 166 subjects was calculated (effect size medium=0.30; alpha=0.05; 1–beta=0.95), and considering a drop-out rate of 15%, a total sample size of 190 patients was determined. 

Statistical analysis will be performed with R version 3.5.3 (The R Project, Vienna, Austria), and epidemiological data will be evaluated. Continuous variables will be described with the mean, standard deviation, median, minimum, maximum, and the 25th and 75th percentiles. Categorical variables will be described with percentages and absolute frequencies. The differences in continuous variables between the two groups will be evaluated with the Kruskal-Wallis test, followed by the Dunn multiple comparison test. The differences between the two diagnostic groups (psychiatric versus neurological diagnosis) for normally distributed data will be evaluated with a one-way analysis of variance (ANOVA), followed by the Newman-Keuls multiple comparison test. The normality of the distribution will be evaluated with the Kolmogorov-Smirnov test. Any correlation between the variables under evaluation will be assessed by the Spearman r correlation. To compare qualitative data, we will use the Chi-square test with the Yates correction or the Fisher exact test. Lastly, the variables will be grouped to their diagnostic groups according to the 10th edition of the International Statistical Classification of Diseases and Related Health Problems or the fifth edition of the Diagnostic and Statistical Manual of Mental Disorders, and a confirmative factor analysis will be done comparing these groups with the prosodic parameters.

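### The abstract and Textbox 1 disagree on excluding neurological speech disorders, which leaves the psychiatric-versus-neurological speech contrast open to bias

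*Protocol article*

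**What the plan says.** **Groups.** Under Study Design and Data Protection, the first step is that "the participants will be grouped by the physician or psychotherapist into a control group (participants without mental disorders) or a case group". The abstract gives the source population: "Inclusion criteria are a neurological or psychiatric diagnosis made by a specialist". Textbox 1 likewise admits outpatients with either kind of condition. Statistical Methods names the comparison: "The differences between the two diagnostic groups (psychiatric versus neurological diagnosis".

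**Eligibility.** The abstract states: "Exclusion criteria include psychosis, dementia, speech or language disorders in neurological diseases, addiction history". The exclusions in Textbox 1 are schizophrenia, dementia, substance abuse now or within a year, a suicide attempt now or within a year, and other comorbidity that the investigator judges significant. No item names a speech or language disorder. The text below the box explains two of the exclusions by their influence on speech: "both schizophrenia and dementia have shown indications".

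**PHQ-D.** Study Design and Data Protection says: "For documentation purposes, the presence or absence (in the case of neurological outpatients) of any psychiatric diagnosis will be screened using the PHQ-D". The abstract's objective and Research Objectives also name the PHQ as one of three questionnaires against which speech is compared.

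**The concern.** The measurement is prosody: intonation, pace, stress and some 200 related parameters. A neurological disorder of speech or language acts directly on these parameters. If such patients enter, they enter mainly as controls, because a neurological patient without a mental disorder can be nothing else in this design. A psychiatric-versus-neurological difference could then reflect neurological speech change in the controls and be read as a marker of mental disorder. A real difference could equally be hidden.

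What is at stake is the group comparison and the second hypothesis, that the analysis can confirm diagnosis and separate syndromes. The primary objective correlates speech parameters with questionnaire scores and does not use the group label. Altered speech could still add unrelated variation to those correlations, or a spurious association if it goes along with distress.

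A second, smaller point concerns the PHQ-D. It screens neurological outpatients for psychiatric diagnoses, but the article does not say what follows when a control screens positive.

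**Working it through.** **1. Who the controls are.** Eligible patients have a psychiatric or a neurological condition (abstract; Textbox 1). Controls are those without a mental disorder (Study Design). That leaves only neurological outpatients, and Statistical Methods labels the two groups accordingly. There is no healthy group.

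**2. The two lists side by side.**

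| Criterion | Abstract | Textbox 1 |
|---|---|---|
| Neurological speech or language disorder | excluded | not listed |
| Psychotic illness | psychosis | schizophrenia |
| German | fluent use | native speaker |
| Substance use | history of addiction, no time limit | abuse now or within 1 year |

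The first row is not the effect of shortening, since the short abstract carries a criterion that the full list lacks. The other three rows are plain inconsistencies about who is eligible and do not by themselves bear on bias in the controls.

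**3. Does another item in Textbox 1 close the gap?** In part. The investigator may exclude for significant comorbidity, and the examples include a recent cerebrovascular event. The same examples appear under good general health as an inclusion criterion. The item is discretionary, and its examples are cancer, cardiac and vascular disease. None is a speech disorder.

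**4. Direction and size of the bias.** Let Δ be the case-minus-control difference in a speech parameter without such patients, q0 and q1 the shares of controls and cases with neurologically altered speech, and δ the mean shift in those patients. The observed difference is then

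Δ + q1·δ − q0·δ = Δ − (q0 − q1)·δ.

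With q0 above q1, the difference moves down if δ is positive and up if δ is negative. Across some 200 parameters both signs are possible. The documents give none of q0, q1 and δ, so no figure can be put on the bias.

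**5. Undetected mental disorder among controls: illustration only.** The plan gives no figure on this point to reproduce. Every input here is an assumption except the total of 166, the two-sided 5% level and the stated "effect size medium=0.30; alpha=0.05", whose index is not named. Suppose a share c of controls truly resembles the average case. The standardised difference d then becomes d(1 − c). In the normal approximation, with an equal split of 83 per group,

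power = Φ(d(1 − c)·√(83/2) − 1.96).

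For d = 0.6 and c = 20%: 0.48 × 6.44 − 1.96 = 1.13, so power is 0.87.

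| Assumed d and split | c = 0 | 10% | 20% | 30% |
|---|---|---|---|---|
| 0.6 (0.30 read as Cohen's f), equal split | 0.97 | 0.94 | 0.87 | 0.77 |
| 0.6, split 1:3 | 0.92 | 0.85 | 0.76 | 0.65 |
| 0.3 (0.30 read as d), equal split | 0.49 | 0.41 | 0.34 | 0.27 |

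The documents state neither the group ratio nor c. Patients whose disorder a specialist missed may be milder than the average case, and then the loss is smaller than shown. The conclusion does not rest on this table.

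**The case against.** The strongest reply concerns the PHQ-D. A reader might infer that it serves documentation alone and that a neurological patient who screens positive must by rule remain a control. The documents support neither reading. The PHQ is also a comparator in the primary objective, and on positive controls the article is silent. A condensed article commonly leaves such handling to the full protocol or analysis plan. This part of the reply stands, and it reduces the PHQ-D point to a suggested sensitivity analysis.

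A reader might also want to define controls as PHQ-D-negative in the main analysis. There are good reasons against that. Cases would need only a clinical diagnosis while controls would also need a clean screen, which can inflate the contrast. A screening questionnaire would overrule a specialist's judgement. A comparator of the primary objective would become part of the group definition.

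The last reply is that the comorbidity item already lets the investigator keep out patients with disordered speech. That holds in part, but a discretionary item that does not name speech cannot replace a criterion that the abstract states outright. The contradiction between the two lists is not something an unseen analysis plan would settle, because eligibility belongs in the protocol.

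**Conclusion.** The point holds as a contradiction in eligibility with a plausible route to bias. Under Textbox 1 as written, patients with neurologically altered speech can enter, mainly as controls. The group contrast and the second hypothesis are therefore open to bias of unknown size and either sign. The primary correlation is exposed less directly.

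This rests on two things that the documents support: the controls are neurological outpatients, and the outcome is prosody. It also assumes that investigators followed Textbox 1 and did not apply the abstract's exclusion in practice.

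A reader might go further and say that the control group is contaminated. The documents do not support that. They report no rate of speech disorder or of undetected mental disorder among controls, and part of the gap is covered by the comorbidity item.

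**What to change.** 1. Reconcile the abstract and Textbox 1 into one eligibility list. It should settle whether neurological speech and language disorders are excluded, and also the wording on psychotic illness, command of German and substance use.
2. Where speech or language status is on record, repeat the group comparison without enrolled participants who have such a disorder. The article does not say that this status is recorded, so the step may be possible only for some participants.
3. Keep the clinician-assigned grouping as the main contrast. Add a sensitivity analysis that removes PHQ-D-positive controls or shows them as a separate comorbid group.
4. Word the group conclusions as psychiatric versus neurological outpatients.

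The cost is small. The first and last steps are wording, and the third uses baseline PHQ-D data that the study already collects. The downside is a little extra analysis and fewer controls, hence less precision, in the sensitivity analyses. By the article's September 2019 status the final calculations had not begun, so the analyses could still be specified beforehand.

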**Figure 1 figure1:**
[figure not shown]
Flowchart of the study protocol. PHQ-D: Patient Health Questionnaire. B5T: Big 5 Test. ADHD-AS: attention deficit hyperactivity disorder-visual analogue scale. SCL-90: Symptom Checklist-90.

### Statistical Methods

It should be possible for the study team to evaluate the efficacy and effectiveness of the raw data from the linguistic analysis in correlation with the clinical data collected with the questionnaires. All statistical tests will be two-tailed and will be considered statistically significant at *P*<.05. A sample size of 166 subjects was calculated (effect size medium=0.30; alpha=0.05; 1–beta=0.95), and considering a drop-out rate of 15%, a total sample size of 190 patients was determined. 

Statistical analysis will be performed with R version 3.5.3 (The R Project, Vienna, Austria), and epidemiological data will be evaluated. Continuous variables will be described with the mean, standard deviation, median, minimum, maximum, and the 25th and 75th percentiles. Categorical variables will be described with percentages and absolute frequencies. The differences in continuous variables between the two groups will be evaluated with the Kruskal-Wallis test, followed by the Dunn multiple comparison test. The differences between the two diagnostic groups (psychiatric versus neurological diagnosis) for normally distributed data will be evaluated with a one-way analysis of variance (ANOVA), followed by the Newman-Keuls multiple comparison test. The normality of the distribution will be evaluated with the Kolmogorov-Smirnov test. Any correlation between the variables under evaluation will be assessed by the Spearman r correlation. To compare qualitative data, we will use the Chi-square test with the Yates correction or the Fisher exact test. Lastly, the variables will be grouped to their diagnostic groups according to the 10th edition of the International Statistical Classification of Diseases and Related Health Problems or the fifth edition of the Diagnostic and Statistical Manual of Mental Disorders, and a confirmative factor analysis will be done comparing these groups with the prosodic parameters.

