### Research Objectives

The primary objective of this study is to evaluate the measurements of the mental state of the participants by comparing the analysis of noncontent speech parameters to the results of several psychological questionnaires (Symptom Checklist-90 [SCL-90], the Patient Health Questionnaire [PHQ], and the Big 5 Test). We hypothesized that the emotional state of mind, the behavioral patterns, the well-being, and some of the personality traits of the participants could be identified using the prosodic analysis algorithm. A second hypothesis is that the diagnosis could be confirmed by the application of the analysis program, and a distinction can be made between different psychopathologically-defined syndromes.

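### A flat P<.05 rule for every test, applied to correlations of over 200 speech parameters with several questionnaires, leaves weak markers indistinguishable from chance

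*Protocol article*

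**What the plan says.** All references are to the protocol article.

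- **Threshold.** Statistical Methods: "All statistical tests will be two-tailed and will be considered statistically significant at" P<.05. The rule covers every test.
- **Speech variables.** Speech Analysis: "This analysis produces raw data of over 200 prosodic parameters for each call". The same section adds: "The raw data parameters will be sent back to the research center for the statistical analysis". No reduction to fewer variables before testing is described.
- **Primary objective.** Research Objectives: "comparing the analysis of noncontent speech parameters to the results of several psychological questionnaires", namely SCL-90, PHQ and Big 5.
- **Correlation method.** Statistical Methods: "Any correlation between the variables under evaluation will be assessed by the Spearman r correlation".
- **Multiplicity procedures.** Dunn after Kruskal-Wallis and Newman-Keuls after ANOVA, both for group differences.
- **Sample size.** "A sample size of 166 subjects was calculated" from "effect size medium=0.30; alpha=0.05; 1–beta=0.95". No allowance for more than one test appears.
- **Occasions.** Under Study Design and Data Protection, SCL-90 and speech are measured at baseline and two follow-ups. The PHQ-D, Big 5 Test and ADHD scale are described as baseline measures.

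**The concern.** The primary objective is to show that speech parameters reflect questionnaire results. A 5% per-test rule applied to a screen of 200 or more parameters yields nominally significant parameters even when speech carries no information about the score. The Dunn and Newman-Keuls procedures do not help. They compare groups within one variable, and the section names only two groups, so they leave untouched the error that accumulates over parameters, scales and occasions. The confirmatory factor analysis listed last relates diagnostic groups to prosodic parameters and does not change the rule for the correlations.

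At stake is how the main result is read. A list of parameters with P<.05 could be reported as evidence for the tool when a list of similar length would be expected by chance.

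**Working it through.** **Inputs.** From the article: two-sided alpha 0.05 per test, 200 parameters (stated as over 200), n=166, effect size 0.30, power 0.95, drop-out 15%. Assumption: the number of scores per questionnaire is not given, so one score is the base case and 5 to 15 scores are shown as a range.

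**1. The plan's own figure.** The type of effect size is not named. Read as one two-sided correlation test (Fisher z):

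n = ((1.960 + 1.645) / atanh(0.30))² + 3 = 138.6, so 139.

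This does not reproduce 166. Variants using Spearman variances give 147 to 152. On the same reading, power at n=166 is Φ(atanh(0.30) × √163 − 1.960) = 0.977. The gap is a separate matter. What counts here is that the calculation uses alpha 0.05 with no adjustment for the number of tests.

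**2. Expected false positives, one score.** 200 × 0.05 = 10. Expectations add whatever the dependence, so this holds for any correlation among parameters.

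**3. Chance of at least one, one score.** If independent: 1 − 0.95²⁰⁰ = 0.99996. Null Spearman simulation at n=166, 600 replicates, with correlated parameters:

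| Structure of the 200 parameters | P(at least one) |
|---|---|
| 20 clusters, within-cluster r 0.6 | 99.5% |
| 20 clusters, r 0.9 | 94% |
| 10 clusters, r 0.9 | 85% |
| one block, all at r 0.9 (extreme) | 30% |

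The mean count stayed near 10 throughout (9.5 to 11.1).

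**4. What passes.** The smallest significant correlation is t / √(n − 2 + t²), with t the two-sided 5% point on n − 2 degrees of freedom.

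- n=166: 1.975 / √(164 + 3.90) = 0.152.
- n=62, the number the Results section reports at the end of the study: 2.000 / √(60 + 4.00) = 0.25.

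For 200 independent null parameters at n=166, the largest |r| has median 0.23 (5th to 95th percentile 0.19 to 0.28). Observed correlations from 0.15 to roughly 0.28 therefore lie within what chance alone produces.

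**5. Several scores, baseline only.** With 5 scores: 1,000 tests, 1,000 × 0.05 = 50 expected. With 15 scores: 3,000 tests, 150 expected. Both counts rest on the assumed number of scores and on every parameter being tested against every score.

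**The case against.** The strongest reply is that only a condensed article is at hand, and that naming a primary pairing or an adjustment is commonly left to the full protocol or SAP. That stands for anything the article merely omits. It does not dispose of the point, because the article states a rule, P<.05 for all tests, and an analysis plan that added error control for the correlations would have to override it.

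Four stronger readings are tempting, and the document does not support them.

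- *False markers are guaranteed.* The probability depends on how correlated the parameters are. The article itself mentions clusters of raw parameters, so independence is doubtful, and the extreme case gives only 30% for one score.
- *The counts for several scores recur at each visit.* Only SCL-90 and speech are repeated. The ADHD scale applies to ADHD cases and is not in the primary objective.
- *No positive result could be interpreted.* Correlations clearly above the null maximum, about 0.28 at n=166 under independence, would still be informative.
- *True power is about 0.6 instead of 0.95.* That figure (0.61) applies Bonferroni over 200 tests and assumes that 0.30 is a correlation. The article does not say so, and 166 is not reproduced on that reading. The remedy below does not use Bonferroni.

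It is also fair to say that the article never lists which variables are crossed, so the full grid is an inference. The one-score case needs only the raw parameters and one questionnaire score.

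**Conclusion.** The point holds in limited form. The stated rule does not fit a screen of more than 200 parameters. Following it gives about 10 expected false positives per questionnaire score when there is no association, under any correlation structure. At least one is virtually certain under independence and likely under the clustered structures examined (about 85–99%). The consequence is that weak or marginal markers, those not far above |r| = 0.15 at n=166, cannot be separated from chance. Strong correlations are not discredited.

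The conclusion assumes that the returned raw parameters are tested individually, as the text implies. It does not depend on the number of scales. Larger totals do, and they apply at baseline only.

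**What to change.** Before the final analysis:

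1. Replace the flat P<.05 rule for the parameter-by-scale correlations with Benjamini-Hochberg false discovery rate control at 5% within each questionnaire, and label these results exploratory. Say whether the SCL-90 family includes the two follow-ups.
2. Name one primary test at two-sided 0.05. One option is baseline SCL-90 overall distress against a single speech score. The definition of that score, or the cross-validated procedure that builds it, should be fixed before the questionnaire data are linked. The existing clusters cannot simply be assumed to serve: Speech Analysis links them to personality scales, not to SCL-90 distress, and does not describe them as locked.
3. State that alpha 0.05 and power 0.95 refer to that single test only.

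The cost is a few sentences of analysis wording and no new data. The downside is that fewer parameters will be nominally significant. Choosing one primary score also narrows an objective that names three questionnaires, so the sponsor should make that choice explicitly.

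### Post-hoc tests are attached to two-group contrasts where they add nothing, the syndrome hypothesis has only a factor analysis that does not compare syndromes, and the two-group test rules overlap.

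*Protocol article*

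**What the plan says.** The Statistical Methods section names two comparisons of continuous variables, each between two groups.

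- The first: "The differences in continuous variables between the two groups will be evaluated with the Kruskal-Wallis test, followed by the Dunn multiple comparison test". It carries no condition on the distribution.
- The second contrasts the two diagnostic groups ("psychiatric versus neurological diagnosis) for normally distributed data will be evaluated with a one-way analysis of variance") and is "followed by the Newman-Keuls multiple comparison test". It applies only to normal data.
- The check on that condition: "The normality of the distribution will be evaluated with the Kolmogorov-Smirnov test". Whether the Lilliefors correction is used is not said.

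The design has two groups: "This study is a case-controlled study with a case group and a control group" (Study Design and Data Protection). The second hypothesis under Research Objectives goes further, expecting that "a distinction can be made between different psychopathologically-defined syndromes". The only method named for several diagnostic groups comes at the end of Statistical Methods, after variables are grouped by ICD-10 or DSM-5: "a confirmative factor analysis will be done comparing these groups with the prosodic parameters".

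**The concern.** Post-hoc procedures are for three or more groups. Here they are attached to the contrasts that have two and are absent from the one that has several. A team that follows the text would run two redundant tests. For the second hypothesis it would fit a model whose result does not say whether any speech parameter differs between, for example, two syndromes.

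The choice of two-group test is also not settled. Taken literally, a normally distributed parameter qualifies for both Kruskal-Wallis and ANOVA. The Study Design section describes controls as participants without mental disorders, and links absence of a psychiatric diagnosis to neurological outpatients. Case versus control and psychiatric versus neurological may therefore be largely the same contrast, with two tests assigned to it. If the Kolmogorov-Smirnov result is meant to decide between them, the method can change from one parameter to the next, over more than 200 parameters.

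**Working it through.** The plan gives no figure of its own on this point. Inputs: two groups per contrast, N=166, two-sided alpha 0.05 (Statistical Methods); more than 200 prosodic parameters (Speech Analysis). Assumptions: n=83 stands for half of 166, since no allocation is given; skewness 1 is an illustration, since no distribution is given for any parameter.

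**1. Dunn after Kruskal-Wallis, two groups.** Without ties, with mean ranks R1 and R2:
- Dunn: z = (R1 − R2) / √[ N(N+1)/12 × (1/n1 + 1/n2) ].
- Kruskal-Wallis: H = 12/[N(N+1)] × (n1·n2/N) × (R1 − R2)².
- Since n1·n2/N = 1/(1/n1 + 1/n2), H = z². A chi-square on 1 df is a squared normal, so the p-values are the same.
- Check on 300 simulated data sets with N=166, with and without ties: largest p-value difference 1e-12 between Dunn and Kruskal-Wallis, and 1e-15 between Dunn and the rank-sum test without continuity correction.

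**2. Newman-Keuls after ANOVA, two groups.** The studentized range statistic is q = √2·|t| and F = t², so both give the t-test p-value. Largest difference in 60 data sets: 3e-14.

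**3. Multiplicity adjustment within a contrast.** The number of pairs is k(k−1)/2. For k=2 this is 1, so nothing is adjusted. For k=4 it would be 6 and for k=6 it would be 15. The article does not give the number of syndromes.

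**4. The factor analysis.** A confirmatory factor analysis asks whether a stated loading pattern reproduces the covariances among variables. It does not by itself test equality of speech parameters between groups, and it measures no discrimination. If all parameters entered, 166 subjects would give a sample covariance matrix of rank at most 165 for more than 200 variables. That matrix is singular, so ordinary maximum likelihood fitting would fail.

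**5. The normality check.** Rejection rates at 5%, by simulation, with mean and SD estimated from the data and a gamma distribution with shape 4 (skewness 1):

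| n | Plain Kolmogorov-Smirnov | With Lilliefors correction |
|---|---|---|
| 166 | about 24% | about 86% |
| 83 | about 6% | about 55% |

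Repeat runs differ by one or two percentage points. On normal data the plain test rejected 0% of samples, so uncorrected it is very conservative.

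**6. Consequence for inference.**
- Type I error of the gated two-group procedure, 3,000 runs each: 5.2% for normal data (83/83), 5.3% for an exponential (83/83), 5.0% for gamma(4) split 120/46.
- Power at a 0.5 SD shift, gamma(4), 83/83: about 89% for the t-test or ANOVA, about 93% for the rank-sum test, a loss of 4 percentage points.

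**The case against.** The strongest reply is that the redundant tests change no result: Kruskal-Wallis and ANOVA are valid with two groups. That stands. This part is a specification error, not a bias. Nor does the article claim that Dunn or Newman-Keuls controls multiplicity over the speech parameters. A reader might infer it, since no other multiple-comparison procedure is named, but the text does not say so.

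A method is named for the syndromes, so it would be wrong to say that they go unanalysed. A multi-group factor model with a mean structure could compare latent means, and an unseen analysis plan may describe one. The article, however, fixes a factor analysis and states no comparison of parameters between syndromes, so the objection narrows the point without removing it.

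Two stronger readings are not supported:
- **That the Kolmogorov-Smirnov test would pass nearly everything as normal.** The correction may be in use, and even the plain test detects strong skewness: at n=166 about 86% for skewness 1.5 and 99.9% for skewness 2; at n=83 about 31% and 83%.
- **That Newman-Keuls inflates the family error rate here.** Its weakness appears with four or more groups, and the article applies it to two.

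**Conclusion.** The point holds in three parts of unequal weight. The main one is that the second hypothesis is tied to an analysis that, as described, would not answer it. This rests on the text and needs no assumed number. Next, the rule for choosing the two-group test is ambiguous and possibly data-driven. Its cost is analyst discretion and, in the skewness-1 example, about 4 points of power; type I error stays near 5%. The size of this part depends on which variant of the normality test is used and on the real distributions, neither of which the article gives. Last, Dunn and Newman-Keuls are redundant where they stand, and deleting them alters no p-value. The correction is worth making before the final analysis.

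**What to change.** - **Syndrome hypothesis:** add to, or substitute for, the factor analysis a Kruskal-Wallis test across the ICD-10/DSM-5 groups, with Dunn pairwise comparisons adjusted by Holm. List the groups in advance. If the factor analysis stays, say what question it answers.
- **Two-group contrasts:** prespecify one test, the rank-sum test, for every continuous parameter. Remove the normality gate, Dunn and Newman-Keuls there. State whether case versus control and psychiatric versus neurological are one contrast or two.
- **Across parameters:** Holm over syndrome pairs within one parameter does not cover the 200 or more parameters. At P<.05, 200 × 0.05 = 10 nominally significant results would be expected per contrast if no parameter differed. This needs its own rule.

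The cost is wording in the analysis section; no new data are needed. The article expected final calculations by November 2019, after this text was written. Where a parameter is truly normal, rank tests have efficiency 0.955 relative to the t-test, a loss of about 5% (1 − 0.955 = 0.045). The number of patients per syndrome is not given, so some pairwise comparisons may be imprecise; intervals should accompany the p-values.
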